## Methods/Design

This research project has 2 stages.

### Stage 1

This part of the study is completed and addressed the first research question [39]. It aimed to identify factors that would influence involvement of relatives not known to have Paget's disease in a programme of genetic screening and preventive treatment. Stage 1 employed semi-structured interviews developed to elicit CS-SRM constructs and to form a basis for developing an Illness Perception Questionnaire [32] for individuals suffering from Paget's disease. It also employed Theory of Planned Behaviour (TPB)-based interviews [40], with their relatives who had not been diagnosed as suffering from Paget's disease to elicit beliefs about the consequences of the behaviours of accepting testing and treatment, about the views of important others regarding these behaviours and about whether these behaviours were easy or difficult for the respondent. The results of Stage 1 have been used to inform the development of this protocol and the questionnaire for Stage 2.

### Stage 2

This part of the study is the focus of this protocol. The Stage 2 has been reviewed and approved by Lothian Research Ethics Committee 1 (ref: 07/S1101/13). It will comprise a postal questionnaire study of people without Paget's disease but who are relatives of people with Paget's disease. This part of the study will address the second research question.

Two sets of individuals will be identified:

(1) Relatives of Paget's patients *with *a family history of Paget's disease (i.e. known history of Paget's disease in more than one blood relative);

(2) Relatives of Paget's patients *without *a known family history of Paget's disease (i.e. known history of Paget's disease in only one blood relative).

This stage aims to quantitatively assess the effect of a range of factors on the acceptability of a programme of genetic testing and preventive treatment in families with and without a family history of Paget's disease. The questionnaire is likely to consist of several measures: illness representations (as measured by the Brief Illness Perception Questionnaire [33]); treatment representations (as measured by a TPB-based questionnaire informed by Stage 1 [39]); a series of dependent variables exploring the acceptability of testing and treatment and the feasibility of a clinical trial of preventive treatment; questions collecting descriptive and demographic details; and questions exploring family environment and beliefs of other family members.

Data will also be collected from probands to describe the disease presentation and its distribution within a family.

The data from questionnaires completed by relatives will be analysed along with available data on members of the family with diagnosed Paget's disease (probands and other affected family members).

### Participants and recruitment

Individuals with Paget's disease will be identified, in the first instance, from two established cohorts: The PRISM trial and The Paget's Disease Family Register (PDFR). Probands and relatives from the PDFR cohort, and probands from the PRISM cohort, have previously given their consent to future contact regarding Paget's disease research (see Table 1 for additional details of how these individuals were approached).

**Table 1 T1:** Approach to potential participants to invite them to participate in the GaP study

	**PRISM**	**PDFR**	**Edinburgh**	**NARPD**
**Probands**	Approach directly (after consultation with caring physician)	Approach directly (after consultation with caring physician)	Approach directly (after consultation with caring physician)	Approach directly
**Relatives**	Approach via proband	Approach directly (after consultation with caring physician)	Approach via proband	Approach via proband

We can identify in total, 254 probands with a family history of Paget's disease, and 1020 individuals without a family history of Paget's disease from these cohorts.

#### The PRISM Cohort

The PRISM cohort involves 1331 patients with Paget's disease from 39 collaborating centres ranging in size from 3 trial participants to approx 250 trial participants. Twenty of these centres have agreed to allow us to approach their patients for this study. We already know from the baseline evaluation that approximately 172 individuals in PRISM have a family history of Paget's disease, whereas 1020 individuals do not.

#### The Paget's Disease Family Register (PDFR)

We will also enrol participants with a family history of Paget's disease from the PDFR. This register currently comprises 49 probands and their affected and unaffected relatives from around the world. Families for this study have been enrolled from the UK [16]. These participants have already taken part in genetic mapping studies that resulted in the identification of *SQSTM1 *mutations as a cause of Paget's disease [3,8]. New families are being included on an ongoing basis and these figures are subject to change.

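### The comparison of families with and without a family history is partly confounded with recruitment cohort, and cohort is not among the listed explanatory variables

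*Protocol article*

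**What the plan says.** Under Methods/Design, Stage 2 defines two sets of relatives by family history and aims to assess what affects "acceptability of a programme of genetic testing and preventive treatment in families with and without a family history of Paget's disease". The Sample Size section plans a random sample of 200 probands for each set.

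The sources of the two sets differ:

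- **Register.** The PDFR section says "We will also enrol participants with a family history of Paget's disease from the PDFR" and "This register currently comprises 49 probands and their affected and unaffected relatives from around the world". It adds "These participants have already taken part in genetic mapping studies", and says that new families keep joining and the figures may change.
- **PRISM.** The cohort section gives "approximately 172 individuals in PRISM have a family history of Paget's disease, whereas 1020 individuals do not". It also says "Twenty of these centres have agreed to allow us to approach their patients for this study", out of 39.
- **Combined pool.** Participants and recruitment gives "254 probands with a family history of Paget's disease, and 1020 individuals without a family history of Paget's disease from these cohorts".
- **Route.** For PDFR relatives, Table 1 has "Approach directly (after consultation with caring physician". PRISM relatives are approached through the proband, who supplies their contact details.
- **Earlier consent to contact.** PDFR probands and relatives gave it. In PRISM only the probands did.

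The sections on explanatory variables cover illness representations, Theory of Planned Behaviour constructs, respondent characteristics and disease presentation in the affected relative. The Analysis section describes multiple and logistic regression built up from these groups. None of these sections names source cohort, recruitment route or previous genetic participation.

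**The concern.** One of the dependent variables is intention to accept a genetic test if offered. Earlier voluntary participation in genetic research on the same disease is plausibly related to that intention, and the register brings it into one of the two sets only. The recruitment route also differs between the register and PRISM, so the two sets differ in more than family history.

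If relatives in the family-history set report higher intention, the reason could be family history, or it could be the way part of that set was assembled. The model as described does not separate the two. The pooled acceptability in the family-history set is affected in the same way. The article intends its results to inform the feasibility of a testing programme and the rationale for a later prevention trial.

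**Working it through.** **1. The plan's own sample-size figures.** The rule is 50 + 8m with m = 26: 50 + 208 = 258 relatives. The inflation factor at cluster size 2 and correlation 1 is 1 + (2 − 1) × 1 = 2, which gives 516. Probands to approach: 516 / (2 × 0.70) = 368.6, rounded up to 369. All three figures reproduce. None of them is a power calculation for the family-history contrast.

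**2. Where each set comes from.** The combined count without a family history (1020) equals the PRISM count (1020), so every identified proband in that set is from PRISM. For the family-history set, 172 from PRISM plus 49 from the register is 221. The article states 254, and the remaining 33 are unexplained. Register growth is one possible reason.

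**3. Register share w of the family-history probands.**

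| Reading | Calculation | w | Register probands among 200 |
|---|---|---|---|
| The 33 are not register families | 49/254 | 19% | 39 |
| The 33 are ignored | 49/221 | 22% | 44 |
| The 33 are register families | 82/254 | 32% | 65 |

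Assume instead that PRISM yields in proportion to its agreeing centres: 172 × 20/39 = 88. Then w = 49/(88 + 49) = 36%, or 82/(88 + 82) = 48%. The family-history pool would be about 137 or 170, below the planned 200, so the whole register would be used. Centres range from 3 to about 250 trial participants, so the proportional yield is only a rough assumption.

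**4. Shift in the comparison.** Let d be the difference in acceptability, in percentage points, between PDFR and other family-history relatives. With equal numbers of relatives per proband, the family-history mean moves by w × d, and so does its unadjusted difference from the other set. The documents give no value for d, so the values below are assumptions.

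| d | w = 19% to 32% | w = 36% to 48% |
|---|---|---|
| −5 | −1.0 to −1.6 | −1.8 to −2.4 |
| +10 | +1.9 to +3.2 | +3.6 to +4.8 |
| +20 | +3.9 to +6.5 | +7.1 to +9.6 |

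If register families returned two to three times as many relatives as PRISM families (assumption), the register share of relatives would run from 32% to 74% over the same readings, and the shift would grow with it.

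**5. Can the two be separated?** Yes. On the stated figures 68% to 81% of family-history probands are not from the register. With two sets of equal size, the correlation between family history and register membership is about 0.33 at w = 19% and 0.56 at w = 48%. The variables overlap but are not aliased.

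**6. Price of separating them.** With n relatives per set and equal variances, the variance factor is 2/n for the pooled contrast and 1/(n(1 − w)) + 1/n for the contrast within PRISM. The ratio of standard errors is √[(1/(1 − w) + 1)/2]:

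- w = 0.193: √[(1.239 + 1)/2] = 1.06
- w = 0.482: √[(1.931 + 1)/2] = 1.21

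The increase is therefore about 6% to 21%.

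**The case against.** Five points can be put against this.

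**Direction.** A reader might infer that acceptability in the family-history set will be overstated. The documents do not support that. No section reports higher intention among register families. Direct approach bypasses the proband's choice of which relatives to name, and PRISM probands are asked for relatives who may like to take part, which could raise intention on the PRISM side. PRISM probands are also research participants who agreed to further contact. This objection stands: the net sign is open.

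**Separability.** A reader might also infer that the design cannot distinguish family history from cohort. PRISM alone holds about 172 probands with a family history and 1020 without, so it can. This too stands: the confounding is partial, and the gap lies in the described model.

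**Role of family history.** It appears under the study aim as part of one factor among several, and no primary between-set contrast is declared. The number of affected relatives and the relationship to them are already listed variables. That limits the weight of the point. Family history nevertheless defines the two sampled sets, so the comparison will naturally be made.

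**Level of detail.** Covariates can be left to an analysis plan that is not shown. That is fair for cohort, which the study office will know for every family. It does not cover a question on previous genetic participation, which cannot be recovered later if relatives are never asked. The variable groups that the article does list, followed as written, leave the comparison confounded in part.

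**Wording of the facts.** The family-history-negative set is PRISM-only for the probands identified so far. Table 1 and the contact section allow other cohorts if response is poor. New register families are still joining, and the article does not say that these took part in mapping. Both limits are accepted here, and both are further reasons to record the source.

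**Conclusion.** The concern holds as partial confounding. An unadjusted family-history comparison, and the pooled acceptability in the family-history set, may be biased by 0.19d to 0.32d on the stated figures, and by 0.36d to 0.48d under proportional centre yield. An upward bias through earlier genetic participation is plausible, but d is unknown even in sign, so the tabulated shifts illustrate scale and are not evidence of bias. They also assume equal numbers of relatives per proband in the two cohorts and leave the usable number of UK register families unresolved. Since the overlap within PRISM lets the problem be handled in the analysis, this is an inexpensive improvement and not a flaw that invalidates the study.

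**What to change.** - Add source cohort (PRISM, PDFR and any cohort added later) to the explanatory variables and to the regression.
- Report the family-history comparison within PRISM families as a sensitivity analysis. This is not identical to the cohort-adjusted model. In that model register relatives still inform the coefficients of shared predictors, and an added cohort containing both kinds of family would inform the family-history coefficient.
- Report acceptability separately for PDFR relatives.
- If feasible, add one item to the relatives' questionnaire on previous genetic testing or sample donation for Paget's disease.
- Reconcile 254 with 172 + 49, and say whether the PRISM counts refer to all 39 centres or to the 20 that agreed, so that the register share is known.

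**Cost.** One variable that the study office should already hold, one further model and possibly one question. The standard error of the family-history contrast rises by about 6% to 21% under the assumptions above, and by more if register families return more relatives than PRISM families. Cohort also adds to the 26 predictors: each additional term raises the plan's own minimum by 8 relatives, or 16 after the inflation factor of 2.

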### Identifying and Contacting Participants

In the first instance, probands will be identified from both the PRISM and PDFR cohorts. For the PRISM cohort, all participants who have died, become unwell or who have withdrawn from the PRISM study are recorded on the PRISM database, and these participants will not be contacted for this study. For the PDFR cohort, every attempt will be made to avoid making inappropriate contact using a variety of methods. For example, where possible the status of probands will be checked with their caring physician/consultant.

If there is a high non-response from the PDFR and PRISM cohorts, we will identify probands from additional cohorts.

#### Contacting PRISM probands

Probands identified from the PRISM cohorts will be contacted by post. A letter will be sent to all probands together with a study information leaflet, inviting them to complete a questionnaire. Probands will also be asked to provide contact details of relatives over the age of 18 who may also like to participate. PRISM probands have previously been asked if they are happy to be contacted about new research projects, and only those agreeing to this will be contacted.

#### Contacting relatives of PRISM probands

A letter will be sent to relatives identified by probands together with a study information leaflet, inviting them to complete a questionnaire.

#### Contacting probands and relatives from the PDFR cohort

A letter will be sent to probands and relatives identified from the PDFR together with a study information leaflet, inviting them to complete a questionnaire.

### Questionnaire reminders

Non-response will be interpreted as a desire not to take part in the study. If no response has been received by the study office (Aberdeen) or Chief Investigator's office (Edinburgh) to the initial mailing, participants will not receive any subsequent questionnaire reminders or further contact from the study office.

### Sample Size

Given that most of these individuals have already engaged in research, we anticipate a high participation rate and estimate that 70% of probands will have living blood relatives and will be happy to contact their relatives. Based upon the experience of a recent study of familial hypercholestorolaemia [41] it is anticipated that an average of 2 relatives per participating proband will participate. The recommended minimum sample is calculated as 50 + 8 m, where m is the number of predictor variables [42]. This study has a total number of 26 predictor variables and the minimum sample size required is 258 relatives.

We anticipate that there will be a clustering effect of responses within families. The size of clustering effect is determined by the intra cluster correlation, and the sample size needs to be inflated to reflect this correlation [43]. We have no prior evidence of the possible size of this clustering effect, so assuming that the study has an average cluster size of 2 relatives per proband and that the correlation was 1 (the worst case scenario), the inflation factor would be 2. We therefore intend to recruit a minimum of 516 relatives to account for this effect. To achieve this it will be necessary to approach a minimum of 369 probands (accounting for 70% participation rate). We intend to approach a random sample of 200 probands with a known family history of Paget's disease, and 200 without.

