### Measures

A questionnaire will be sent to probands. This questionnaire will include:

• Details of disease presentation in the proband;

• An overview of the family structure;

• Details of relatives to contact.

A questionnaire will be sent to first and second-degree relatives of probands. This questionnaire will include specific measures of:

• All variables hypothesised to affect the likelihood of uptake of a programme of genetic testing and preventive treatment (potential explanatory variables; see section 6.1); and

• Dependent variables measuring the acceptability or intention to take up an offer of a programme of genetic testing and preventive treatment.

In addition, each section of the questionnaire will have a section of open questions.

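### The inflation factor of 2 is a worst case only for equal family sizes, or for a family-weighted analysis with 2 as the mean among families that respond

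*Protocol article*

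**What the plan says.** All of the sizing is in the Sample Size section of the protocol article.

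- Base size: "The recommended minimum sample is calculated as 50 + 8 m, where m is the number of predictor variables". Then: "This study has a total number of 26 predictor variables and the minimum sample size required is 258 relatives".
- Average family size, first mention: "it is anticipated that an average of 2 relatives per participating proband will participate". In the clustering step: "assuming that the study has an average cluster size of 2 relatives per proband". No spread or range is given.
- Clustering: "We have no prior evidence of the possible size of this clustering effect". The section therefore takes the extreme: "the correlation was 1 (the worst case scenario), the inflation factor would be 2".
- Result: at least 516 relatives, from at least 369 probands approached at 70% participation. The plan is to approach 400 (200 with and 200 without a family history). The 70% describes probands who have living blood relatives and are willing to contact them.

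Three other sections bear on how family sizes will vary. Under Measures, "A questionnaire will be sent to first and second-degree relatives of probands", with no number per family fixed. On the Paget's Disease Family Register: "This register currently comprises 49 probands and their affected and unaffected relatives from around the world". Under Questionnaire reminders, non-responders are not contacted again. The Analysis section names multiple and logistic regression and does not say how families are weighted.

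**The concern.** The plan has no evidence on within-family correlation, so the 516 rests entirely on being sufficient at the most extreme correlation. The formula that gives a factor of 2 assumes clusters of equal size, whereas the text supplies only an average. Family sizes can be expected to differ: all adult first- and second-degree relatives are eligible, some are mailed directly and others only if the proband names them, and there are no reminders.

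There is a second gap. At correlation 1 each family contributes one independent observation, so the limiting quantity is the number of families with a responding relative. The target counts relatives. The average is also first stated per participating proband, and a proband can take part without any relative returning a questionnaire.

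At stake is whether 516 gives the protection against clustering that the text attributes to it. The most exposed predictors are those shared by a whole family, such as the disease-presentation variables collected from the proband.

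**Working it through.** **1. The plan's own figures**

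- Base size: 50 + 8 × 26 = 258.
- Equal-cluster factor: 1 + (m − 1) × ICC = 1 + (2 − 1) × 1 = 2.
- Relatives: 258 × 2 = 516.
- Probands: 516 / (2 × 0.70) = 368.6, rounded up to 369.
- Planned approach: 400 × 0.70 = 280 participating probands, and 280 × 2 = 560 relatives expected.

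Every stated figure reproduces.

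**2. Unequal families, each relative weighted equally**

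For a family-level predictor the factor is 1 + ((1 + CV²) × m − 1) × ICC, where CV is the standard deviation of family size divided by its mean. At ICC = 1 and m = 2 this is 2(1 + CV²), which is also Σm²/Σm. The CV is not in the document, so the values below are assumptions. The last column is the largest ICC at which 516 still gives 258.

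| CV | Factor at ICC = 1 | Effective N from 516 | Largest ICC covered |
|---|---|---|---|
| 0 | 2.00 | 258 | 1.00 |
| 0.25 | 2.13 | 243 | 0.89 |
| 0.5 | 2.50 | 206 | 0.67 |
| 0.7 | 2.98 | 173 | 0.51 |
| 1.0 | 4.00 | 129 | 0.33 |

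Two concrete patterns with mean 2:

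- Families of 1, 2 and 3 in equal number: (1 + 4 + 9)/(1 + 2 + 3) = 2.33; 516 / 2.33 = about 221.
- Families of 1 and 3 in equal number: (1 + 9)/(1 + 3) = 2.50; 516 / 2.50 = about 206 (simulation: 204).

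**3. The same families, weighted by family**

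If 2 is the mean among families with at least one responding relative, 516 / 2 = 258 families at any spread. In the 1-and-3 example a family-weighted analysis recovers about 258 (simulation: 256).

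**4. If the average counts probands with no responding relative**

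Take Poisson(2) as an assumed pattern. The share of probands with at least one responding relative is 1 − e⁻² = 0.865.

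- 516 relatives come from 516/2 × 0.865 = about 223 families.
- The 400 planned probands give 280 × 0.865 = about 242 families.

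Both are below 258, and weighting cannot repair this. More generally, 258/280 = 92% of participating probands must have at least one responding relative for the planned approach to deliver 258 families.

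**5. Less extreme correlations, person-weighted**

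- ICC 0.3, CV 1.0: factor 1 + (4 − 1) × 0.3 = 1.9; 516 / 1.9 = 272.
- ICC 0.3, CV² = 0.5: factor 1 + (3 − 1) × 0.3 = 1.6; 516 / 1.6 = about 322.
- ICC 0.5, CV² = 0.5: factor 1 + (3 − 1) × 0.5 = 2.0; 516 / 2.0 = 258.

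At ICC = 1, the expected 560 relatives cover a person-weighted analysis up to a CV of about 0.29: 560 / (2 × 1.084) = 258.

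**The case against.** A reader might infer that the factor of 2 fails unless every family supplies exactly two relatives, or that 516 necessarily falls short. The document supports neither. With 2 as the mean among contributing families, 516 relatives are 258 families whatever the spread, and a family-weighted or cluster-model analysis uses them fully. The article does not commit to equal weighting of relatives, and that detail may properly sit in an analysis plan that is not shown. The size of any shortfall rests on a CV that the document does not give.

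The empty-family route also depends on a reading. The clustering step speaks of an average cluster size, and a family with no respondent is arguably not a cluster. Against that, the earlier sentence ties the average to participating probands, and the 70% covers only having relatives and being willing to contact them. The text leaves the base open.

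A reader might further infer that mailing would stop once 516 relatives had replied. No such rule is stated: 516 is a minimum, 400 probands are to be approached, and further cohorts are held in reserve if non-response is high. Nor is there an arithmetic slip.

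Finally, a correlation of 1 is a deliberate extreme, and predictors that vary within families (illness perceptions, age, own health) are usually less affected. All of this limits the weight of the point. It does not make the unqualified worst-case label correct.

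**Conclusion.** The point holds in a limited form. At correlation 1 the factor of 2 is sufficient under either of two conditions: equal family sizes, or an analysis that weights by family (or models the cluster) with 2 as the mean among responding families. The Sample Size section states neither, yet presents the factor as the worst case.

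Outside those conditions, the effective N at correlation 1 would be about 221 for assumed families of 1, 2 and 3 in a person-weighted analysis. Under an assumed Poisson(2) that includes empty families, the number of families would be about 223 from 516 relatives, or about 242 from the planned 400 probands. These figures illustrate the gap; they do not predict it.

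The practical weight is modest. At an ICC of 0.3 or below, 516 still gives at least 258 effective observations for CV up to 1.0. What needs correcting is a stated property of the sample size that the design does not guarantee.

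**What to change.** In the Sample Size section:

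- Remove the unqualified worst-case label. Either state the conditions under which a factor of 2 suffices at correlation 1, or state what 516 covers in a person-weighted analysis, for example an ICC up to about 0.5 if CV² is 0.5.
- State that the mean of 2 refers to families with at least one participating relative.
- Alongside the 516 relatives, track the number of families with at least one participating relative against 258.

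The cost is a few reworded sentences and one additional recruitment count. No extra enrolment is needed. The downside is that the stated robustness to clustering becomes less favourable.
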